### Security endpoints

Safety and toxicity assessment will be calculated based on AEs, vital signs, clinical laboratory tests, and electrocardiograms. Each AE will be monitored during the study, and its nature, intensity and relationship with treatment will be evaluated.

## Statistical analysis

A full analysis set will be used to analyse the primary and secondary efficacy indicators. The full analysis set refers to the ideal subject set, which is as close as possible to intention-to-treat principles (the main analysis should include all subjects). For missing value estimation of the main variables, the last observation carried forward (LOCF) method will be used to carry forward the missing data of the study, and the number of subjects whose efficacy is evaluated at the endpoint will be consistent with that at the beginning of the study. The safety set is the main group of safety evaluations in this study. All groups with at least one study drug (cell preparation) and at least one safety assessment record will constitute the safety set of this study.

All statistical tests will be conducted using unilateral tests, and *P* < 0.05 will be considered to be statistically significant (except when specifically stated). Measurement data will be statistically described by the mean, median, standard deviation, maximum, minimum, and 25 and 75% quantiles; counting data or grade data will be expressed as the frequency. FPS, TTP and OS will be estimated by the Kaplan-Meier method and compared between groups with an unstratified log-rank test. Greenwood’s formula will be used to calculate 95% CIs. Fisher’s exact probability method will be used to compare the incidence of ORR, DCR and AEs between the two groups. The Wilcoxon rank-sum test will be used to compare the significant differences between the two groups for adverse reactions of different degrees. Changes in laboratory test results and quality of life assessments during the study will be summarized in tables and graphs. In addition, the relationship between abnormal changes and cell preparation will be further analysed.

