### Trail design

The study protocol (Issue date: 9 September 2017, protocol amendment number: v1.2) was written in accordance with the Standard Protocol Items: Recommendations for Interventional Trials (SPIRIT) 2013 Statement [25]. A SPIRIT checklist is provided in the supplementary material (Additional file 1: Table S1). This early exploratory phase I/II clinical trial was initiated by the investigators and supported by the key research and development special funding of the Jiangsu Science and Technology Bureau for social development. The affiliated Hospital of Jiangsu University is responsible for clinical research.

The study was designed as a prospective, randomized, open-label, controlled phase I/II parallel-group trial to explore the efficacy and safety of NKT cell infusion immunotherapy combined with gefitinib versus gefitinib monotherapy in patients with advanced EGFR-mutated NSCLC (Fig. 1). This study will recruit 30 participants with advanced NSCLC who meet the inclusion/exclusion criteria and individually randomize them at a 1:1 ratio based on the trial schedule (Fig. 1). The two arms of the trial are as follows (Table 1):
Experimental group (Arm A): 250 mg gefitinib orally once daily. After being effectively treated with gefitinib for 8 weeks, allogeneic NKT cell transfer treatment will be added every 4 weeks, with a total cell number of 1 × 10^10^ ± 15% divided into two infusions with an interval of 3 days. This process will be repeated for a total of 16 weeks, which is defined as one-cell therapy cycle, and then NKT cell infusion treatment will be suspended for 4 weeks. After that, this cycle will be continually repeated three times (total of 60 weeks) or stopped when disease progression/unacceptable toxicity/participant choice occurs (Table 1).Control group (Arm B): 250 mg gefitinib orally once daily until disease progression/unacceptable toxicity/participant choice occurs.

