### Randomization

After the subjects are registered (and before any trial treatment), the subjects will be randomly assigned to the experimental group (Arm A) or the control group (Arm B) at a proportion of 1:1. The method of block randomization will be used to randomize the subjects into the groups. The random number table will be generated by statistics experts.

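### As worded, the safety set requires the cell preparation, which excludes the whole gefitinib-only arm and contradicts the planned between-group adverse event tests

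*Protocol article*

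**What the plan says.** All references are to the protocol article.

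- **Population.** Statistical analysis, first paragraph, on the safety set: "The safety set is the main group of safety evaluations in this study". Its entry rule follows: "All groups with at least one study drug (cell preparation) and at least one safety assessment record will constitute the safety set".
- **Tests.** The next paragraph of that section says that Fisher's "exact probability method will be used to compare the incidence of ORR, DCR and AEs between the two groups". For severity: "The Wilcoxon rank-sum test will be used to compare the significant differences between the two groups for adverse reactions of different degrees".
- **Treatment by arm.** Trail design gives the control arm "250 mg gefitinib orally once daily until disease progression/unacceptable toxicity/participant choice occurs", with no cells. For the experimental arm: "After being effectively treated with gefitinib for 8 weeks, allogeneic NKT cell transfer treatment will be added every 4 weeks". Table 1 puts the first infusion in weeks 9–12.
- **Timing of randomization.** Randomization says: "After the subjects are registered (and before any trial treatment), the subjects will be randomly assigned". Table 1 agrees, showing randomization in the week 0–8 block. Table 2, however, lists freedom from progression after eight weeks of gefitinib among the inclusion criteria.

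**The concern.** The entry rule and the tests do not fit together. The rule ties membership of the main safety population to a product that only Arm A receives, while the tests need both arms. This is not a detail left to an analysis plan, because the article states both the population and the tests.

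Safety is one of the trial's two stated aims. Arm A takes gefitinib as well as cells, so judging which events the cells add depends on seeing what happens on gefitinib alone. A safety population without Arm B gives up that comparison. The trial is also open-label: if the denominator stays ambiguous, someone will have to choose it when events by arm may already be known.

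**Working it through.** **Inputs.** 15 patients per arm, 30 in total (Study population). Gefitinib only in Arm B; cells in Arm A after eight weeks of gefitinib (Trail design, Table 1). One-sided tests at 0.05 (Statistical analysis). The share of Arm A leaving before the first infusion is not given, so 5% to 20% is assumed.

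**Step 1: the plan's own figure.** 30 patients at 1:1 gives 15 + 15, as stated. The number rests on a rule of thumb, so there is no power calculation to reproduce.

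**Step 2: who qualifies under the literal rule.** Arm A: at most 15. Arm B: 0, since none receives cells.

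**Step 3: what the tests do with 15 against 0.** With x events in Arm A and an empty Arm B, only one table has the observed margins. Its hypergeometric probability is C(15,x)·C(0,0)/C(15,x) = 1. Running Fisher's test at x = 0, 5, 10 and 15 gave p = 1 each time. It can never reject, and the rank-sum test has no second sample to rank.

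**Step 4: other readings of the sentence.**

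| Reading of the entry rule | Arm A | Arm B |
|---|---|---|
| Cell preparation required (literal) | up to 15 | 0 |
| Gefitinib or cells | up to 15 | up to 15 |
| Cells in Arm A, gefitinib in Arm B | up to 15, less those never infused | up to 15 |

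The planned two-group tests favour the second or third reading. The section's closing intention to relate abnormal changes to the cell preparation fits the first. The text does not settle it.

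**Step 5: patients lost before the first infusion (conditional).** If randomization comes before the eight gefitinib weeks, any rule requiring an infusion drops Arm A patients who leave in that period. With early-loss proportion d, the expected loss is 15d and the chance of losing at least one is 1 − (1 − d)^15.

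| Assumed d | Expected loss of 15 | Chance of losing at least one |
|---|---|---|
| 5% | 0.75 | 1 − 0.95^15 = 54% |
| 10% | 1.5 | 1 − 0.90^15 = 79% |
| 20% | 3 | 1 − 0.80^15 = 96% |

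If the eight-week no-progression criterion in Table 2 is met before randomization, this loss should be small.

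**Step 6: after correction.** With up to 15 against 15, both tests can be run. As an illustration only, assume event rates of 50% in Arm A and 10% in Arm B, tested one-sided for an excess in Arm A. Fisher's test at 0.05 then rejects with probability about 67%, against 0 under the literal rule.

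**The case against.** The strongest reply is that the sentence was never meant literally. It speaks of groups in the plural, the section uses that word for the arms, and a one-arm set would make the next paragraph pointless. The parenthesis may be shorthand for study drug or cell preparation. This is plausible as intent, and it stands as a reason to treat the point as a drafting error. It does not remove the error, because no other part of the article redefines the set.

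It can also be said that the safety set is called the main population, not the only one, and that the adverse event tests are not tied to it by name. That is correct, but no other safety population is offered.

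A reader might infer that control-arm adverse events will not be collected, or that the comparison is impossible. The article does not support this. Its Assessments and Security endpoints sections do not limit monitoring to cell recipients, so the data should exist, and the fault lies in the set definition.

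A reader might also take early loss in Arm A as established, and size it by treating the 9–12 months to resistance in the Background as a median PFS. Under an exponential model, eight weeks (1.84 months) gives 1 − 0.5^(1.84/9) = 13% to 1 − 0.5^(1.84/12) = 10%. The Background figure describes when resistance develops and is not given as a median PFS. The exponential shape is not in the article either, and the sum ignores withdrawal for toxicity or by choice. The Table 2 criterion may also remove most of this loss.

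**Conclusion.** The sentence is wrong as written: the stated entry rule defeats a stated analysis. Its size on the literal reading is complete, at most 15 patients against 0, and that conclusion needs no assumption about dropout or event rates. The full analysis set, and so the efficacy analyses, are untouched, as is data collection.

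The early-loss issue is secondary and conditional. It arises under Trail design, Table 1 and the Randomization section, and would be small if the Table 2 criterion is applied before randomization. The article does not give its size; the 0.75–3 of 15 above rests wholly on an assumed 5–20%. An infused-only Arm A set against all controls would be lopsided, but the article does not propose that comparison, so it is a risk of a careless repair and not a fault of the plan.

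**What to change.** 1. Redefine the safety set as all randomized patients in both arms who received at least one dose of any study treatment (gefitinib or cells) and have at least one safety record. Name it as the population for the Fisher and Wilcoxon adverse event tests, over the whole study.
2. Show Arm A patients who never received cells as a clearly labelled category. Do not pool them with controls, as a plain grouping by treatment received would do.
3. Report adverse events from the first infusion in the cell-exposed subset as a separate descriptive table. It should not replace the between-arm comparison, because the subset is selected by what happened after randomization if randomization precedes the gefitinib weeks.
4. Reconcile Trail design, Table 1 and Randomization with the eight-week criterion in Table 2, so that it is clear whether patients can be lost between randomization and first infusion.

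Items 1 to 3 cost one reworded sentence, one labelled category and one extra table. They need no new data and no change in conduct. Item 4 asks only that the passages be made to agree; which timing applies is for the investigators to state.

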
This is also an exploratory study to test the safety and efficacy of the intravenous infusion of CD8 + CD56+ NKT cells, which replicates a planned larger study in at a smaller scale. Some authors have put forward suggestions on the sample size of pilot trials, specifically, 10 [26], 12 [27], or 15 [28] per group and a total of at least 20 participants [29]. According to a sample size “rule of thumb” of 30, the number of patients was designated as 15 patients in the experimental group and 15 patients in the control group, with a total sample size of 30 patients in this study. Although the power of this study is inadequate for evaluating clinical efficacy, the estimation of the efficacy of NKT cell immunotherapy combined with gefitinib and gefitinib alone will enable follow-up studies to calculate the efficacy more accurately.

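### With 15 patients per arm the planned one-sided Fisher test is valid but conservative; naming Boschloo's exact test for ORR, DCR and AE incidence would be a cheap, minor gain, mainly at mid-range rates

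*Protocol article*

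**What the plan says.** The Statistical analysis section of the protocol article makes one-sided testing the general rule: "All statistical tests will be conducted using unilateral tests", with P "< 0.05 will be considered to be statistically significant" unless stated otherwise. For the binary outcomes it names Fisher's test: its "exact probability method will be used to compare the incidence of ORR, DCR and AEs between the two groups".

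The Study population section fixes the size at "15 patients in the experimental group and 15 patients in the control group". This rests on a rule of thumb, not on a calculation. The same section concedes low power ("Although the power of this study is inadequate for evaluating clinical efficacy") and gives estimation for follow-up studies as the purpose. ORR and DCR are secondary endpoints. The article gives no expected ORR, DCR or AE rate and no power for these comparisons.

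**The concern.** Fisher's test conditions on the total number of events. With 15 per arm each total allows few possible P-values, so the test usually stops well short of the 5% it may spend. An unconditional exact test can use more of that allowance without breaking the limit.

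The stake is avoidable loss of power in a 30-patient trial. For ORR, a real difference is missed more often than the plan's own threshold requires. For AEs, conservatism is not automatically the safe direction: an imbalance of 7/15 v 2/15 gives P = 0.054 by Fisher and 0.028 by Boschloo, at the same permitted error.

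**Working it through.** **Inputs from the article.** 15 per arm (Study population); one-sided P < 0.05 and Fisher's test (Statistical analysis). There is no stated power or sample-size derivation to reproduce.

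**Assumptions.** The event rates are mine, since none are given. The one-sided alternative is taken as a higher rate in the experimental arm.

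**Method.** All 16 × 16 possible tables (a events of 15 v b of 15, total t = a + b) were enumerated.

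- Fisher: P(a,b) = Σ over j ≥ a of C(15,j)·C(15,t−j) / C(30,t); reject if P < 0.05.
- Boschloo: use the Fisher P as the statistic. Its P-value is the maximum, over the unknown common rate π, of the probability of all tables with a Fisher P no larger than the one observed; reject if this is < 0.05.
- True error at π: Σ over rejected tables of Bin(a;15,π)·Bin(b;15,π). Power is the same sum with the two arms' own rates.

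**Example, 7/15 v 2/15 (t = 9).** Numerator: 6435·105 + 6435·15 + 5005·1 = 675,675 + 96,525 + 5,005 = 777,205. Denominator: C(30,9) = 14,307,150. Fisher P = 0.054; Boschloo P = 0.028. The table 13/15 v 8/15 gives the same pair by symmetry.

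**Size at 15 v 15.** Fisher has a maximum of 2.16%; it is 1.2% at π = 0.1 or 0.9, and 0.26% at 0.05 or 0.95. Boschloo has a maximum of 4.95%, at π = 0.5, and rejects when the Fisher P is at or below about 0.084. It drops none of Fisher's rejections and adds nine tables: 5v1, 7v2, 8v3, 9v4, 10v5, 11v6, 12v7, 13v8 and 14v10.

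**Power at 15 v 15 (rates assumed).**

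| Rates | Fisher | Boschloo | Gain (points) |
|---|---|---|---|
| 50% v 80% | 0.373 | 0.520 | 14.7 |
| 30% v 60% | 0.359 | 0.508 | 15.0 |
| 60% v 90% (or 10% v 40%) | 0.463 | 0.592 | 12.9 |
| 60% v 80% | 0.191 | 0.300 | 10.9 |
| 70% v 90% | 0.256 | 0.353 | 9.7 |
| 70% v 95% | 0.435 | 0.522 | 8.7 |
| 80% v 95% (or 5% v 20%) | 0.186 | 0.226 | 4.0 |
| 90% v 98% | 0.042 | 0.044 | 0.2 |
| 0% v 20% | 0.352 | 0.352 | 0.0 |

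The last row follows directly. With no control events both tests first reject at 4/15 v 0/15, where Fisher P = C(15,4)/C(30,4) = 1365/27405 = 0.0498, so both powers equal P(X ≥ 4) for Bin(15, 0.2).

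**Sample-size equivalent.** Fisher matches Boschloo's power at 15 per arm with 19 per arm (50% v 80%), 20 (60% v 90% and 70% v 95%) or 22 (30% v 60%).

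**Unequal arms.** At 15 v 14 Fisher's maximum size is 3.1%, and the gain at 30% v 60% falls to 2 to 5 points, depending on which arm is smaller. Elsewhere the gain can rise. If only the arm of 15 has events, 4/15 v 0/14 has Fisher P = C(15,4)/C(29,4) = 1365/23751 = 0.0575; Fisher misses this table and Boschloo rejects it.

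**Mid-P.** Mid-P Fisher has the same rejection region as Boschloo at 15 v 15, but not at 15 v 14.

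**The case against.** The strongest reply is that nothing here is an error. P < 0.05 is a decision threshold; a test whose true error stays below 5% is a valid 5%-level test, and Fisher is a standard choice for 30 patients. A reader might infer from the 2.2% that the plan misstates its significance level. The documents do not support that: they promise a threshold, not an attained error of 5%. This part of the reply stands in full.

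A reader might also infer that ORR, DCR and AEs all lose 9 to 15 points. They do not. That range belongs to mid-range rates, which are assumptions. DCR may well sit near 100%, because Table 2 requires no progression after 8 weeks of gefitinib, and AEs specific to the cells should be close to absent in a control arm that receives no infusions. At 15 v 15 the gain there is 0 to 4 points.

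Nor does it follow that the plan conceals harm. The nature, intensity and relationship to treatment of each AE are also evaluated, and severity is compared by a Wilcoxon test.

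Two practical points also stand. The safety set depends on receiving study treatment and having a safety record, so AE denominators may differ from 15 v 15. And the change more than doubles the false-positive rate at a common rate near 50% (about 2.2% to 4.95% per comparison) in a plan that states no multiplicity control.

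None of this favours Fisher at the plan's own level. Boschloo rejects every table that Fisher rejects, so it never has less power, and it respects the same limit. Conceding low power is no reason to give up more of it.

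**Conclusion.** The point holds as a minor, inexpensive improvement. At 15 v 15 Fisher uses at most 2.2% of the 5% the plan allows, and Boschloo uses up to 4.95%. The gain is about 9 to 15 points of power at assumed mid-range rates and 0 to 4 points near 0% or 100%. The sizes are exact for 15 v 15; the powers rest on assumed rates, and both change with unequal arms.

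The weight is modest. These are secondary and safety comparisons in a trial that presents itself as exploratory, and power remains limited after the change: about 30% to 59% for the 20- to 30-point differences in the table.

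**What to change.** In the Statistical analysis section, replace Fisher's test by Boschloo's exact unconditional test for ORR, DCR and AE incidence, at the stated threshold, and list Fisher P-values as a secondary column. Name Boschloo specifically: mid-P Fisher coincides with it at 15 v 15 but not at 15 v 14. Make the change before the comparison is run; switching after seeing a Fisher P of 0.054 would not be credible. The article reports data collection as ongoing.

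The cost is one sentence and a standard software call, with no new data or patients. The downsides are a less familiar test and a higher false-positive rate per comparison, within the 5% allowed.

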**Fig. 1 Fig1:**
[figure not shown]
Flow diagram of this parallel randomised trial. EGFR: epidermal growth factor receptor; PFS: progression-free survival; TTP: time to progression; ORR: overall response rate; DCR: disease control rate; OS: overall survival

**Table 1 Tab1:** Treatment schedule for the frequency of gefitinib and NKT cell in both arms of the trail

Week-4-0	Week 0–8			One cell therapy cycle				
				Week 9–12	Week 13–16	Week 17–20	Week 21–24	Week 25–28
Screening	Randomization	Experimental group (Arm A)	Donor selection, PBMCs^a^ acquisition and NKT cell preparation	NKT infusion	NKT infusion	NKT infusion	NKT infusion	Suspend
			Gefitinib orally once daily					
		Control group (Arm B)	Gefitinib orally once daily					

This schedule use one cell therapy cycle as an example, and the follow-up treatment is carried out according to the same cell therapy cycle until the trial is terminated after the disease has progressed or complete three cell therapy cycles (total 60 weeks). ^a^*PBMCs* peripheral blood mononuclear cells

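### Adverse events are tested between arms as crude proportions, although observation time may end at progression and so differ with PFS

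*Protocol article*

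**What the plan says.** The Statistical analysis section of the protocol article names two between-arm comparisons for adverse events: Fisher's exact test is applied "to compare the incidence of ORR, DCR and AEs between the two groups", and "The Wilcoxon rank-sum test will be used to compare the significant differences between the two groups for adverse reactions of different degrees". Neither has a time component. In the same section PFS, TTP and OS are handled by Kaplan-Meier and log-rank methods, so unequal follow-up is recognised for efficacy.

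The Trail design section sets when treatment ends. Cell therapy in Arm A runs for a "total of 60 weeks) or stopped when disease progression/unacceptable toxicity/participant choice occurs". Arm B receives "250 mg gefitinib orally once daily until disease progression/unacceptable toxicity/participant choice occurs", with no limit in weeks. The note to Table 1 says treatment continues "until the trial is terminated after the disease has progressed or complete three cell therapy cycles (total 60 weeks").

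On the recording period, Security endpoints says "Each AE will be monitored during the study, and its nature, intensity and relationship with treatment will be evaluated", and Assessments likewise refers only to the course of the study. No section says whether recording stops with treatment, at progression or at a fixed date.

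**The concern.** Comparing the share of patients with an AE is a fair comparison of toxicity only if the arms are observed for similar lengths of time. Here the length may be set by progression, and the trial is meant to delay progression. The arm with longer PFS would then have more time to collect events at the same underlying rate, and the crude proportion could not separate a higher rate from longer observation.

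The Objectives section makes safety, with efficacy, the basis for deciding whether the combination deserves further study. The safety reading should not move with the PFS result. Conversely, patients who leave early because of progression or their own choice have less time in which later AEs can be seen, and this can dilute a real difference.

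**Working it through.** The article gives no AE rate, expected exposure or power for AEs, so there is no figure of its own to reproduce. The size below rests on assumptions.

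**Inputs**
- Control median time to progression: 10.5 months, the mid-point of the 9 to 12 months to resistance given in Background. This gives μ = ln 2 / 10.5 = 0.0660 per month.
- Observation limit F: 8 weeks of gefitinib plus 60 weeks of cell therapy cycles = 68 weeks, or 15.6 months.
- AE hazard λ: 0.05 per month, equal in both arms (assumed; range 0.02 to 0.10).
- PFS hazard ratio (HR): 0.7 to 0.5 (assumed; the article states none).
- AE recording ends at progression or at F (assumed).

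**Formula.** Crude incidence = λ / (λ + μ·HR) × [1 − exp(−(λ + μ·HR)·F)].

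**Same limit in both arms, equal AE hazard**
- Arm B: 0.05/0.1160 × [1 − exp(−1.810)] = 0.431 × 0.836 = 36.0%.
- Arm A, HR 0.7: 0.05/0.0962 × [1 − exp(−1.501)] = 0.520 × 0.777 = 40.4%.
- Arm A, HR 0.5: 0.05/0.0830 × [1 − exp(−1.295)] = 0.602 × 0.726 = 43.7%.

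The false excess is 4 to 8 points, about one patient in 15 at the upper end. At λ = 0.02 the figures are 17.2% against 19.5% and 21.2%. At λ = 0.10 they are 55.7% against 61.4% and 65.7%. The range is therefore 2 to 10 points. Events per patient-month have an expected ratio of 1.0 in every case.

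**Effect on the test.** Exact enumeration of the one-sided Fisher test at 0.05 with 15 against 15, for control incidences of 30% to 50%, control medians of 9 or 12 months and a 68-week limit in both arms, gives these rates of declaring Arm A more toxic when the hazards are equal:
- equal PFS: 2.0% to 2.2%
- HR 0.7: 3.1% to 4.5%
- HR 0.5: 4.3% to 7.5%

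**Limit in Arm A only.** With no limit in Arm B, its incidence is 0.05/0.1160 = 43.1%, against 40.4% (HR 0.7) and 43.7% (HR 0.5) in Arm A. The excess reverses or vanishes. With a control median of 12 months and control incidence of 30%, HR 0.7 gives 24% in Arm A.

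**Early stops in Arm A.** Let the true AE hazard in Arm A be 1.5 times higher (0.075) and raise the stopping hazard 1.5-fold to 0.0990.
- Extra stops are for progression or choice: 0.075/0.1740 × [1 − exp(−2.715)] = 40.2%, against 36.0% in Arm B. Without the extra stops Arm A would show 0.075/0.1410 × [1 − exp(−2.200)] = 47.3%. The 11-point difference shrinks to 4.
- Extra stops are for toxicity: the AE that causes the stop is counted. If it lies within the 0.075, Arm A shows 47.3%. If it is additional (0.0330), Arm A shows 0.1080/0.1740 × [1 − exp(−2.715)] = 58.0%. The signal of 11 to 22 points remains.

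**The case against.** Four objections carry weight.

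- **The recording window is not stated.** AE recording is described only as lasting through the study. The Table 1 note suggests that it ends at progression or after three cycles but does not settle it. If both arms were followed for AEs to a common date regardless of progression, most of the bias would go. This stands, and it makes the finding conditional.
- **The effect is modest.** Table 2 requires no progression after 8 weeks of gefitinib. Giving both arms that progression-free period (1.84 months, then the same hazards) changes the figures to 40.1% against 43.6% and 46.2%, an excess of 3 to 6 points. The false-positive rates above stay near the nominal 5%. The article also assesses each AE's relation to treatment and sets no AE-based decision rule. This stands and lowers the severity.
- **Crude proportions are usual in a 30-patient exploratory trial, and a SAP may add exposure-adjusted rates.** This stands in part. The article does not merely leave the method open: it names the crude comparison as the test.
- **Stronger readings go too far.** A reader might infer that the arm with longer PFS must look more toxic. The documents do not support that, because the Arm B sentence has no limit in weeks and the direction can reverse if only Arm A is limited. A reader might also infer that a product toxic enough to make patients stop early would look safe. That fails, because unacceptable toxicity is itself an AE and enters the count. Only other or later AEs are cut off.

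**Conclusion.** The point holds in a limited form. The article tests AE incidence without regard to time, while its own stopping rules make observation time plausibly dependent on PFS. With a common 15.6-month limit and equal hazards of 5% per month, the false excess in Arm A is about 4 to 8 points for a PFS hazard ratio of 0.7 to 0.5, or 2 to 10 points over hazards of 2% to 10% per month. This rests on AE recording ending with treatment, exponential times, and an assumed AE rate and PFS effect. Early stops for progression or choice can hide later AEs; stops for toxicity do not make the product look safe. Severity is minor to moderate: the bias is small against the noise of 15 per arm, but foreseeable and cheap to avoid.

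**What to change.** In Statistical analysis:

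1. State one AE observation window, defined in the same way for both arms, and reconcile it with the Table 1 note and the Arm B sentence in Trail design.
2. Base the between-arm comparison on time to first AE and time to first grade 3 or higher AE. Give cumulative incidence curves with death and progression-related end of observation as competing events, and compare cause-specific hazards. Both are needed: cumulative incidence shows the burden patients experience but still moves with PFS, whereas the cause-specific hazard compares rates among those still observed.
3. Add events per patient-month in each arm, with the rate ratio and its interval, using person-time over that same window.
4. Keep crude proportions as description.

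The cost is wording and modest programming, with no extra patients or visits. It assumes that AE onset dates and end-of-observation dates are collected, which the article does not state. The drawbacks are wide intervals at 15 per arm and, for per-month rates, the assumption of a roughly constant hazard.
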